## Abstract

**Background:**

Gamma Knife radiosurgery (GKRS) is increasingly applied in patients with multiple brain metastases and is expected to have less adverse effects in cognitive functioning than whole brain radiation therapy (WBRT). Effective treatment with the least negative cognitive side effects is increasingly becoming important, as more patients with brain metastases live longer due to more and better systemic treatment options. There are no published randomized trials yet directly comparing GKRS to WBRT in patients with multiple brain metastases that include objective neuropsychological testing.

**Methods:**

CAR-Study B is a prospective randomised trial comparing cognitive outcome after GKRS or WBRT in adult patients with 11–20 newly diagnosed brain metastases on a contrast-enhanced MRI-scan, KPS ≥70 and life expectancy of at least 3 months. Randomisation by the method of minimization, is stratified by the cumulative tumour volume in the brain, systemic treatment, KPS, histology, baseline cognitive functioning and age. The primary endpoint is the between-group difference in the percentage of patients with significant memory decline at 3 months.

Secondary endpoints include overall survival, local control, development of new brain metastases, cognitive functioning over time, quality of life, depression, anxiety and fatigue. Cognitive functioning is assessed by a standardised neuropsychological test battery.

Assessments (cognitive testing, questionnaires and MRI-scans) are scheduled at baseline and at 3, 6, 9, 12 and 15 months after treatment.

**Discussion:**

Knowledge gained from this trial may be used to inform individual patients with BM more precisely about the cognitive effects they can expect from treatment, and to assist both doctors and patients in making (shared) individual treatment decisions. This trial is currently recruiting. Target accrual: 23 patients at 3-months follow-up in both groups.

**Trial registration:**

The Netherlands Trials Register number NTR5463. ClinicalTrials.gov registration number NCT02953717, first received October 27, 2016, 8 patients were enrolled in this study on 31 July 2017.

## Background

Brain metastases (BM) are the most common tumours in the central nervous system, and account for 20% of cancer deaths each year [1]. Twenty to 40% of all cancer patients develop one or multiple BM during the course of their illness [2]. If left untreated, these patients display a median survival of only one or two months [3, 4]. Most BM originate from lung, breast, skin, kidney, gastrointestinal tract, lymphoma, and prostate [1, 5, 6]. The incidence of BM is thought to be rising as a result of the growing elderly population and advances in cancer treatments which prolong life, allowing for BM to develop [2, 7–10].

Most patients with BM already have cognitive deficits prior to BM treatment due to the BM itself, epilepsy or medication use (i.e., corticosteroids, anti-epileptic drugs, chemotherapy, other systemic therapies) [11–13]. Whole brain radiation therapy (WBRT) has long been the mainstay of treatment for patients with BM [14, 15]. However, its use has decreased in recent years due to advances in radiation technology and growing concerns regarding the often persistent adverse effects after 6–24 months on cognitive function (e.g., memory, attention and concentration impairments as measured with objective neuropsychological tests) [9, 16–18]. Meanwhile, treatment has diversified and stereotactic radiosurgery (SRS) is increasingly employed in the management of (multiple) BM to spare healthy tissue and thereby aiming to prevent cognitive side effects [16, 19, 20].

Due to increased efficacy of systemic cancer treatments there is a growing number of patients with BM that live long enough (i.e., > 6 months) to experience radiation-induced brain injury, including cognitive decline [21, 22]. Because cognitive functions are essential for our daily social, occupational and personal life, and are related to therapy compliance and quality of life in general, a full understanding of the cognitive side effects of radiotherapy is essential.

Traditionally, radiation-induced brain injury is divided into three categories: acute, early delayed, and late delayed [23–25]. Acute and early delayed injury (after 1–6 months) are thought to be of a transient nature. Late delayed injury (after 6–24 months) on the other hand is usually more severe and irreversible. Patients with late delayed effects most often exhibit progressive impairments in memory, visual motor processing, problem solving ability, and attention, all of which can be very debilitating in daily life. It has been demonstrated that the extent of delayed cognitive impairment correlates positively with the total dose received and with the time-dose-fractionation scheme [12, 16].

Radiation-induced brain injury can result from direct neurotoxic effects or indirectly through metabolic abnormalities, microvascular changes, enhanced cytokine gene expression, persistent oxidative stress and inflammatory processes [24, 26, 27]. In addition, radiation therapy may, disrupt hippocampal neurogenesis, which may, in turn, negatively affect memory and learning functions [28, 29].

Among patients with 1–4 BM, the use of SRS has received widespread acceptance and is supported by prospective data [19, 30]. In addition, SRS has been proven effective as the initial treatment option for patients with multiple BM: Mostly for patients with 5–10 BM, but also for patients with > 10 BM and even for patients with > 20 BM [31–37]. Yamamoto and colleagues conducted a case-matched study comparing treatment results after SRS for patients with 2–9 versus > 10 BM. Approximately 90% of all patients died of extracranial disease, regardless of the number of BM. Survival times did not differ significantly between groups. It was concluded that these carefully selected patients with > 10 BM (controlled primary cancer, no extracerebral BM, better KPS scores, and higher RPA class) might be favourable candidates for SRS alone [33].

Additionally, according to the US guideline on BM there is growing evidence suggesting that cumulative tumour volume in the brain is a better selection criterion for SRS than the number of BM [38]. Accordingly, guidelines no longer specify an upper limit for the number of brain metastases [38, 39].

In comparison to WBRT, SRS has the better ability to spare healthy tissue because of the high level of precision and the quick dose fall-off. Therefore, treatment with SRS is expected to cause fewer cognitive side effects than WBRT. However, there are no published trials yet directly comparing SRS alone versus WBRT alone, that include objective neuropsychological testing. This prospective randomised study (CAR-Study B), will yield information on which treatment modality, Gamma Knife radiosurgery (a form of SRS) or WBRT, best preserves cognitive function in patients with 11–20 BM, as assessed with reliable and valid neuropsychological tests. These tests are recommended by the International Cognition and Cancer Taskforce (ICCTF) [40]. Knowledge gained from this trial may possibly change clinical practice and international guidelines on BM.

This randomised trial is one of the two Cognition and Radiation studies (The CAR-Studies: CAR-Study A and B). CAR-Study A is a longitudinal trial assessing cognitive functions after Gamma Knife radiosurgery (GKRS) alone in patients with 1–10 BM (Clinicaltrials.gov identifier: NCT02953756).

### Objectives

CAR-Study B aims to assess, in a randomised design, change in cognitive performance after treatment with either GKRS or WBRT in patients with multiple (11–20) BM.

The primary objective is to determine the between-group difference in the percentages of patients with significant cognitive decline at 3 months after treatment as assessed by the Hopkins Verbal Learning Test-Revised (a memory task). The primary hypothesis is that the percentage of patients with reliable cognitive decline at 3 months will be significantly higher after treatment with WBRT in comparison to GKRS, in patients with 11–20 newly diagnosed BM.

### Secondary outcome measures

Cognitive functioning over time (max 15 months)Overall survivalLocal controlDevelopment of new BMPatient Reported Outcomes (PROs)FatigueDepression and anxietyQuality of life

## Methods/design

### Trial design

CAR-Study B is a two-arm randomised trial. Adult cancer patients (*n* = 46), with 11–20 BM, Karnofsky Performance Status (KPS) ≥ 70 and a life expectancy of at least 3 months, are screened for inclusion and exclusion criteria (Table 1) by the radiation-oncologist. Eligible patients are invited for study participation at their first visit at the Gamma Knife Centre. During this first consultation, patients receive an information letter about the study and its procedures.

**Table 1 Tab1:** Eligibility criteria - inclusions and exclusions

Inclusion criteria	Exclusion criteria
• Histologically proven malignant cancer	• Primary brain tumour
• Gadolinium-enhanced volumetric MRI-scan showing 11–20 newly diagnosed BM	• A second active primary tumour
	• Small Cell Lung Cancer, Lymphoma, Leukaemia, Meningeal disease
• Cumulative tumour volume in the brain ≤30 cm^3^	• Prior brain treatment (radiation/surgery)
• Lesion > 3 mm from the optic apparatus	• Upfront planned surgery after GKRS
• Patient age ≥ 18 years	• History of a significant neurological or psychiatric disorder
• Karnofsky Performance Status ≥70	• Participation in a concurrent study in which neuropsychological or quality of life assessments are involved
• Anticipated survival ≥3 months	• Underlying medical condition precluding adequate follow-up
• Patient informed consent obtained (verifying that patients are aware of the investigational nature of this study)	• Patients unable to complete test battery due to any of the following reasons:
• Patients can be undergoing concurrent systemic therapy at the discretion of their treating oncologist	○ Lack of basic proficiency in Dutch
	○ IQ < 85
	○ Severe aphasia
	○ Paralysis grade 0–3 (MRC scale)
	○ Severe visual problems

After signing a written informed consent statement, co-signed by the principle investigator or a formally delegated authorized person, a baseline neuropsychological assessment (NPA) is performed. Subsequently, patients are randomised by the method of minimisation 1:1 to either GKRS (*n* = 23) or WBRT (n = 23). The trial schema and randomisation factors are shown in Fig. 1. The trial has been approved by the local medical ethics review committee (METC Brabant, The Netherlands). Patients from both arms are followed up at 3, 6, 9, 12 and 15 months after treatment. High rates of attrition and noncompliance are very common in trials in patients with metastatic disease [14, 41]. In an attempt to maximize patient comfort and convenience, the administration of the test battery and additional questionnaires is combined with usual care clinical visits on site (3-monthly contrast MRI-scans and consult with the radiation-oncologist).

**Fig. 1 Fig1:**
[figure not shown]
Trial Flow

In both groups, chemotherapy is administered at the discretion of the primary physician and recorded by the research team. Type and duration of systemic therapy, use of steroids and other medication are accurately monitored and registered. Treatment side effects for both arms are recorded according to the National Cancer Institute Common Terminology Criteria for Adverse Events (CTCAE version 4). Patients in both treatment arms may receive additional GKRS or WBRT, or salvage surgery when recurrences occur at any one of successive follow-ups; these additional treatments are recorded.

### Participants

Patients who meet the inclusion and exclusion criteria (Table 1) are eligible for the study. It is projected to include 46 patients.

### Setting

Gamma Knife Centre Tilburg, Department of Neurosurgery, Elisabeth-TweeSteden hospital, The Netherlands.

### Interventions

#### Gamma knife radiosurgery (GKRS)

GKRS is performed with a Leksell Gamma Knife® ICON, Elekta Instruments, AB. Depending upon the volume and location, a dose of 18–25 Gy is prescribed with 99–100% coverage of the target. Dose limits for organs at risk are as follows: brainstem: 18 Gy, optic chiasm or optic nerves: 8–10 Gy.

#### Whole brain radiation therapy (WBRT)

Dose and fractionation scheme will be at the discretion of the treating radiation oncologist (in a tertiary referral hospital dedicated to radiotherapeutic oncology), though most commonly used dose and fractionation schemes are 20 Gy in 5 fractions of 4 Gy (standard schedule in Europe) and 30 Gy in 10 fractions of 3 Gy (occasionally used schedule).

#### Neuropsychological assessment (NPA) and patient-reported outcomes (PROs)

A reliable, valid neuropsychological test battery (Table 2) is used to assess cognitive functioning [40, 42, 43] and is administered by a trained neuropsychologist. In addition, measures of patient-reported outcomes (PROs) are used to assess anxiety and depression, quality of life and fatigue (Table 2). The total time for neuropsychological test administration, including assessment of PROs, ranges from approximately 60 to 90 min.

**Table 2 Tab2:** Neuropsychological test battery and patient-reported outcomes (PROs)

Cognitive Domain	Cognitive Test
Verbal memory	Hopkins Verbal Learning Test-Revised (HVLT-R)
Cognitive flexibility	Trail Making Test B (TMT B)
Word Fluency	Controlled Oral Word Association (COWA)
Working memory	Wechsler Adult Intelligence Scale - Digit Span
Processing speed	Wechsler Adult Intelligence Scale - Digit Symbol
Motor dexterity	Grooved Pegboard (GP)
Patient Reported Outcomes	Questionnaire
Quality of life	Functional Assessment of Cancer Therapy-Brain (FACT-Br)^a^
	• Physical well-being (PWB)
	• Functional well-being (FWB)
	• Social well-being (SWB)
	• Emotional well-being (EWB)
	• Brain Cancer Subscale (BRCS)
Fatigue	Multidimensional Fatigue Inventory (MFI)^a^
	• General fatigue
	• Reduced motivation
	• Physical fatigue
	• Mental fatigue
	• Reduced activity
Anxiety and depression	Hospital Anxiety and Depression Scale (HADS)^b^
	• Anxiety
	• Depression

^a^Published normative data of FACT-Br and MFI are used for the interpretation of quality of life and fatigue scores [55, 56]

^b^A cut-off point ≥8 is used to indicate symptoms of depression or anxiety [57]

### Assessment of outcome

#### Primary endpoint

The primary endpoint is the between-group difference in the percentages of patients with significant memory decline at 3 months after treatment. Memory decline is defined as a 5-point decrease from baseline in HVLT-R Total Recall score, based on a reliable change index (RCI) [44]. This definition is based on the result reported by Chang et al. in 2009 [45].

#### Secondary endpoints

Differences in percentages of patients with a ≥ 5-point decrease in HVLT-R total recall between treatment arms are evaluated at 6, 9, 12 and 15 months as is done for the primary endpoint at 3 months.Group mean scores for all neuropsychological tests and questionnaires are determined for both treatment arms at baseline, 3, 6, 9, 12 and 15 months.Percentages of patients with cognitive impairment are determined at baseline, 3, 6, 9, 12 and 15 months.Overall survival is calculated as the time from the first day of treatment to date of death.The RANO-BM criteria (Response Assessment in Neuro-Oncology Brain Metastases [46]) are used to determine local and distant tumour control.

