### Statistical methods

The Bayesian power analysis and interim analyses are based on the randomised trial by Chang and colleagues [45]. An independent statistician will do interim monitoring of this trial using Bayesian statistical methods [51, 52]. Each patient’s HVLT-R total recall score recorded at 3 months is assigned a binary outcome: A decline in the total recall score of 5 points or greater compared with baseline will be considered a *failure* (0). A stable or improved score, or a decline of 4 points or less compared with baseline will be considered a *success* (1). The failure rate for treatment *k* is designated *qk*. The prior failure rates for both treatment groups will be modelled as Beta(2.09, 2.91)-distributions, with a mean of 0.42 for both groups (for details see Appendix). During the trial, stopping rules specify that in the case of a probability greater than 0.975 for the event that the failure rate of one treatment group is higher than the failure rate of the other treatment group, we will stop randomising patients to that treatment-arm. In this case, the study is terminated prematurely and the central research question will be answered. If the effect sizes are comparable to earlier accounts in the literature (following Chang et al. an effect size of 0.30 is expected), the early stopping rule will likely come into effect when 46 patients are enrolled (23 patients at 3-months follow-up in both groups; for details see Appendix).

Group analyses are carried out on an intent-to-treat principle. Raw cognitive test scores are compared with published normative values according to age (and, if available, to education) and converted into standardized scores. Cognitive impairment is defined as test performance at or below − 1.5 SD from the normative mean [6, 53]. Reliable change indices (RCI), reflecting change at the individual level in the context of observed changes based on published normative data, correcting for measurement errors are calculated, since group results may mask the variability in individual responses to the intervention [44]. Number of patients, who have improved versus the number of patients who remained stable, or declined, will be counted for all follow-up assessments. These will be compared over conditions with chi-square tests.

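### Overall survival is counted from the first day of treatment, not from randomisation, so randomised patients who are never treated have no survival time and the clock can start at different times in the two arms

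*Protocol article*

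**What the plan says.** Under Secondary endpoints the protocol article fixes the origin: "Overall survival is calculated as the time from the first day of treatment to date of death". The abstract lists survival among the outcomes of the randomised comparison: "Secondary endpoints include overall survival, local control, development of new brain metastases".

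Trial design gives the order of events. Consent comes first, then the baseline neuropsychological assessment, and then: "Subsequently, patients are randomised by the method of minimisation 1:1". Treatment follows allocation. Statistical methods states the analysis principle: "Group analyses are carried out on an intent-to-treat principle".

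On place of treatment, the Setting is "Gamma Knife Centre Tilburg, Department of Neurosurgery, Elisabeth-TweeSteden hospital, The Netherlands", while the treating radiation oncologist for WBRT is located "in a tertiary referral hospital dedicated to radiotherapeutic oncology". Trial design also ties the visit schedule to treatment: "Patients from both arms are followed up at 3, 6, 9, 12 and 15 months after treatment".

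The article gives no interval from randomisation to first treatment in either arm, and no rule for the survival time of a patient who is randomised but not treated.

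**The concern.** An intention-to-treat comparison of survival needs a starting date that every randomised patient has and that allocation cannot influence. The date of randomisation meets both conditions. The first day of treatment meets neither: some randomised patients may never reach it, and the date depends on how quickly the allocated treatment can be arranged.

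Two things follow. Deaths and withdrawals between randomisation and treatment leave the survival analysis, possibly in unequal numbers by arm. And the time spent waiting, whatever its length in each arm, is not counted.

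The population makes this more than a formality. Anticipated survival need only be 3 months, the article itself warns that attrition and noncompliance are common in metastatic disease, and with 23 per arm each untreated patient is 1/23 = 4.3% of an arm.

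**Working it through.** **The plan's own figures.** No survival figure is stated, so there is none to reproduce. The only sizing figure concerns the memory endpoint: a probability of 0.975 at 23 per arm with an effect size of 0.30 (Appendix). Failure rates of 0.57 and 0.27 follow from the prior mean of 0.42 plus and minus 0.15. If the observed rates equal these, the posteriors are

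- WBRT: Beta(2.09 + 23 × 0.57, 2.91 + 23 × 0.43) = Beta(15.20, 12.80)
- GKRS: Beta(2.09 + 23 × 0.27, 2.91 + 23 × 0.73) = Beta(8.30, 19.70)

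and the probability that the WBRT rate is the higher is 0.972, close to the stated 0.975. Survival time does not enter this calculation, so the sizing is untouched by the present point. Whether that sizing is adequate is a separate question.

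**Reading the sections together.**

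1. Randomisation precedes treatment (Trial design).
2. Survival starts on the first day of treatment (Secondary endpoints).
3. From 1 and 2, a patient randomised and never treated has no start date, and a death before treatment is not counted.
4. Group analyses are intention-to-treat (Statistical methods), so that patient belongs in the comparison. Statements 2 and 4 cannot both be applied to that patient.
5. The treatments differ, and Setting and the WBRT section point to different sites. The wait can therefore differ by arm, but no section reports it. Length of the WBRT course plays no part, because the first day is the origin.

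**Illustration of how many patients could be lost.** These inputs are assumptions, not figures from the article: exponential survival from randomisation, the same in both arms; median m of 6 or 9 months; wait w of 7 to 21 days; 30.44 days per month.

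Proportion dying before treatment: p = 1 − exp(−ln 2 × w / (30.44 × m)). Expected number in an arm of 23: 23 × p.

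| Median | Wait | p | Of 23 |
|---|---|---|---|
| 9 months | 7 days | 1.76% | 0.40 |
| 9 months | 14 days | 3.48% | 0.80 |
| 9 months | 21 days | 5.17% | 1.19 |
| 6 months | 7 days | 2.62% | 0.60 |
| 6 months | 14 days | 5.17% | 1.19 |
| 6 months | 21 days | 7.66% | 1.76 |

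The range is about 2% to 8% of an arm, or 0.4 to 1.8 patients. Withdrawals before treatment would add to it.

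**Shift in origin between arms.** If GKRS began on day 7 and WBRT on day 14 to 21, the WBRT clock would start 14 − 7 = 7 to 21 − 7 = 14 days later after randomisation. With equal waits the shift is zero; with the waits reversed it changes sign.

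**Effect on the hazard ratio.** Among patients alive at treatment start, survival for a further time t is S(w + t)/S(w). With constant hazard λ this is exp(−λ(w + t))/exp(−λw) = exp(−λt), whatever w is. With the same hazard in both arms and pre-treatment deaths dropped, the hazard ratio is therefore 1.00 even if the waits differ. Bias needs a hazard that changes over time, or selective failure to start treatment. The article gives no data on either.

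**The case against.** The strongest case against is that no bias is shown. No waiting times are reported, and separate scheduling at the WBRT site is an inference from two place descriptions. The eligibility criteria (KPS of at least 70, anticipated survival of at least 3 months) make death before treatment less likely than a constant hazard implies. Every treated patient can still be analysed in the allocated arm, so the conflict with intention-to-treat is confined to those who never start. Counting from treatment also matches the visit schedule, and an analysis plan that is not shown could deal with untreated patients. Survival is one unsized secondary endpoint and will be imprecise in about 46 patients under either origin.

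Most of this stands as a limit on size. It does not remove the defect. The origin is a stated rule, not a detail left open, and an analysis plan that counted from randomisation would contradict the article. Anchoring the cognitive tests to treatment is a separate choice, not questioned here, and it does not require survival to share that origin.

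A reader might go further and infer that the clocks do start at different times, or that the definition yields a spurious hazard ratio obtained by subtracting the wait from the median. The article supports neither. It reports no waits, and the subtraction assumes nobody dies while waiting, which contradicts both an exponential model and the premise that early deaths are dropped. Nor does the article give survival the role of a lead safety check on withholding WBRT; patients in both arms may later receive additional WBRT or GKRS.

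**Conclusion.** The point holds as a defect of definition. The stated origin leaves randomised but untreated patients without a survival time, against the declared intention-to-treat principle, and it allows the clock to start at different times after randomisation in the two arms. The size and direction of any bias cannot be determined from the article, and no hazard ratio should be attached to it.

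The loss of 0.4 to 1.8 patients per arm of 23 rests wholly on the assumed median, wait and constant hazard. It would be smaller if early deaths are rarer than a constant hazard implies, and larger if withdrawals before treatment are included. The primary endpoint, the stopping rule and the total of 46 do not change. The change is worth making because the comparison is randomised and the remedy is nearly free.

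**What to change.** Define overall survival as the time from the date of randomisation to death from any cause, in all randomised patients, analysed as allocated. Report the interval from randomisation to first treatment by arm, with the number never treated. Keep survival from the first day of treatment as a supplementary analysis only.

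The cost is one sentence. Registration and randomisation run through an online system, which should already hold the date. No sample size, visit or patient procedure changes. The article defines no time-to-event endpoint for local or distant control, so nothing needs correcting there; if one is added, it should use the same origin.
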